### Participant timeline

4.4

The participants will be researched for 24 months, from 1st April 2019 to 1st April 2021. The final visit of all participants is scheduled for 31st July, 2021. The recruitment process is shown in Figure 1, and the schedule is shown in Table 2.

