**Table 1 T1:**
[figure not shown]
Components of HGWG.

Anti-rheumatic drugs (DMARDs), such as methotrexate (MTX) and sulfasalazine, may be used during the observation period. Patients’ original records are recorded. Non-steroidal anti-inflammatory drugs (NSAIDs) may be used to control patient's pain. The doctor responsible for the project will keep all medication records during the patients’ treatment. In addition, other conditions and treatments should be documented in the management manual. Both groups will have a 3-month treatment and a 9-month follow-up. At 7 time points (baseline, 2 weeks, 4 weeks, 8 weeks, 12 weeks, 24 weeks, and 48 weeks), visits will be scheduled for each patient. The plan is shown in Table 2.

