### Data collection and monitoring

4.5

This is a 48 weeks’ clinical trial in which participants will receive 12 weeks of medication and 36 weeks of follow-up. Disease activity will be assessed at 7 time points (baseline, 2 weeks, 4 weeks, 8 weeks, 12 weeks, 24 weeks and 48 weeks). Longhua Hospital affiliated with Shanghai University of Traditional Chinese Medicine (http://www.longhua.net/ywsy/gzlc/287.jhtml) is responsible for quality control and training for investigators.

Epidata (version 3.0) procedure will be used to restrict data values. Two trained investigators will enter and compare the data independently to rule out the difference.

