### Statistical analysis

4.6

Trained statisticians will adopt intention-to-treat approach for effectiveness and safety analysis. In addition, the last-observation-carried-forward method will be applied in handling missing values. All statistical analysis will be conducted by Statistical Packages of Social Sciences (SPSS) software (version 22.0). Statistical test is two-sided and *P* < .05 is statistically significant. The mean ± standard deviation will be used for the description of continuous variables. The percentage is used to categorize the variable's description. Continuous variables following the normal distribution will be analyzed by Student *t* test; otherwise, non-parametric tests will be used to compare group differences.

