### Trial status

5.1

The trial will begin on 1st April 2019, and we will complete the recruitment on 1st April 2021.

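### The stated final visit date (31 July 2021) cannot be squared with recruitment to 1 April 2021 and 48 weeks per participant, so late recruits cannot have the week-48 visit and some cannot have week 24

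*Protocol article*

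**What the plan says.** All statements are in the protocol article.

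- **Start (5.1 Trial status):** "The trial will begin on 1st April 2019".
- **End of recruitment (5.1):** "we will complete the recruitment on 1st April 2021".
- **Study period (4.4 Participant timeline):** "The participants will be researched for 24 months, from 1st April 2019 to 1st April 2021".
- **Last visit (4.4):** "The final visit of all participants is scheduled for 31st July, 2021".
- **Time per participant (4.5 Data collection and monitoring):** "participants will receive 12 weeks of medication and 36 weeks of follow-up". Section 2.2 agrees: "Both groups will have a 3-month treatment and a 9-month follow-up". Both sections list seven visits, the last at week 48.
- **Use of the late visits (4.2 Secondary measurements):** ACR20/50/70, DAS28, HAQ-DI, pain, patient global assessment, AIS and SF-36 are all to be compared at weeks 24 and 48.
- **Missing data (4.6 Statistical analysis):** an intention-to-treat approach, and "the last-observation-carried-forward method will be applied in handling missing values".

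Nothing in the article provides for shortened follow-up of late recruits.

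**The concern.** A patient who joins at the end of recruitment needs 48 more weeks, but the calendar stops about four months later. The scheduled week-48 visit, and for the last recruits the week-24 visit, would then fall after the trial's own closing date.

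Treatment ends at week 12, so weeks 24 and 48 are the only visits that can show whether any benefit lasts once treatment has stopped. If those visits cannot take place for some patients, and the carry-forward rule is applied to the gaps, part of the durability evidence would be copies of earlier results. This loss would come from the calendar, not from patients withdrawing, and it can be foreseen before the first patient is enrolled.

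**Working it through.** **Inputs.** Start 1 April 2019 and end of recruitment 1 April 2021 (5.1); final visit 31 July 2021 (4.4); visits at weeks 12, 24 and 48, that is days 84, 168 and 336 (4.5); 120 patients (2.5).

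**Can the stated final visit date be reproduced?** No. 1 April 2021 to 31 July 2021 is 121 days, and 121/7 = 17.3 weeks. That holds the 12-week treatment phase but neither later visit.

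**Visits of a patient recruited on the last day, 1 April 2021:**

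| Visit | Date due | Against 31 July 2021 |
|---|---|---|
| Week 12 (+84 days) | 24 June 2021 | 37 days before: fits |
| Week 24 (+168 days) | 16 September 2021 | 168 − 121 = 47 days after |
| Week 48 (+336 days) | 3 March 2022 | 336 − 121 = 215 days after |

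Reading section 2.2 in calendar months (3 + 9 = 12) would put the last visit at 1 April 2022, which widens the gap slightly.

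**Latest enrolment that still allows each visit:**

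- Week 48: 31 July 2021 − 336 days = 29 August 2020.
- Week 24: 31 July 2021 − 168 days = 13 February 2021.

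**Patients affected.** The recruitment window is 731 days. The article gives no accrual rate, so the counts below are assumptions. With f the fraction of the window that falls too late:

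- Week 48: f = 215/731 = 0.294. Week 24: f = 47/731 = 0.064.
- Uniform accrual gives 120 × f: 35.3 patients (29.4%) at week 48 and 7.7 (6.4%) at week 24.
- Front-loaded accrual, for illustration a rate falling linearly to zero at the end, gives 120 × f²: 10.4 (8.7%) and 0.5 (0.4%).
- Back-loaded accrual, for illustration a rate rising linearly from zero, gives 120 × [1 − (1 − f)²]: 60.2 (50.2%) and 14.9 (12.4%).

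The cut-off dates do not depend on accrual; the counts do.

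**What carry-forward would insert, under uniform accrual.** About 35.3 − 7.7 = 27.6 patients would have week 24 but not week 48. Their week-48 value would be the week-24 value, observed 12 weeks after treatment ended. About 7.7 patients would have neither visit, and their end-of-treatment week-12 value would stand in for both.

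**The case against.** **One date may simply be wrong.** Section 4.4 uses 1 April 2021 as the end of the period in which participants are studied, while section 5.1 uses the same day as the close of recruitment. A slip in a condensed article is a likely cause. That supports an easy correction, but it does not remove the contradiction. If the whole study ended on 1 April 2021, the final visit four months later would conflict with the same section, and 5.1 would still be at odds with both. The figure and table not shown could at most repeat visit weeks that the text already gives.

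**Carry-forward may not be meant for visits that were never due.** Section 4.6 speaks only of missing values, and an analysis plan not shown here could exclude such visits. This stands: that part of the concern is conditional. The conflict of dates does not depend on it.

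**A reader might infer that persistence of effect is bound to be overstated.** The documents do not support that. Most affected patients would carry forward an off-treatment week-24 value, and the rule applies to both arms. Bias towards persistence arises only if the group difference shrinks after the visit carried forward, which nothing in the article establishes. What does hold is that a copied value adds no information on durability.

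**A reader might also add this loss to the 20% allowance in section 2.5.** That allowance belongs to the sample size for ACR50, whose primary time point is week 12. No power target is stated for weeks 24 and 48, and some late recruits would drop out anyway, so the two losses do not simply add.

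**Conclusion.** The contradiction between 4.4, 4.5 and 5.1 is certain and rests on stated dates alone. As written, the week-48 visit is impossible for anyone enrolled in the last 215 days of recruitment, and the week-24 visit for anyone enrolled in the last 47 days.

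The number of patients is less certain. Under uniform accrual the week-48 loss is substantial and the week-24 loss small, so the two should not be described together as a large share. Neither count is firm without an accrual forecast.

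The primary comparison, its sample size and its timing are untouched. The harm is limited to secondary outcomes after treatment, with a possible overstatement of persistence if the group difference fades and the carry-forward rule is applied to visits that could not occur. This should be corrected, but it does not threaten the main result.

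**What to change.** Reconcile sections 4.4, 4.5 and 5.1 in one of these ways. The sponsor must say which date is the intended one.

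1. **Move the final visit** to 3 March 2022 or later, keeping recruitment to 1 April 2021. Cost: 215 days, about seven months, on the calendar.
2. **Correct the end of recruitment** to no later than 29 August 2020, keeping 31 July 2021. Cost: the window falls from 731 to 516 days (731 − 215), about 17 months, so average accrual must rise from 120/24 = 5 to 120/17 = 7.1 patients a month.
3. **If 31 July 2021 is a hard stop and recruitment stays as stated,** specify that week-48 outcomes are analysed in all randomised patients enrolled by 29 August 2020 and week-24 outcomes in all those enrolled by 13 February 2021, with no carrying forward into visits that were never due. Enrolment date is known before allocation, so each subset remains a randomised comparison. Section 4.6 must be amended to match, because this changes the analysis set from all 120 patients under intention to treat. Cost, under uniform accrual and before dropout: about 120 − 35 = 85 patients at week 48 and 120 − 8 = 112 at week 24. Standard errors at week 48 would be about √(120/85) = 1.19 times those with all 120.

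The first two options keep the planned follow-up for everyone. The third needs only a change of text but gives up precision on durability.

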### Data collection and monitoring

4.5

This is a 48 weeks’ clinical trial in which participants will receive 12 weeks of medication and 36 weeks of follow-up. Disease activity will be assessed at 7 time points (baseline, 2 weeks, 4 weeks, 8 weeks, 12 weeks, 24 weeks and 48 weeks). Longhua Hospital affiliated with Shanghai University of Traditional Chinese Medicine (http://www.longhua.net/ywsy/gzlc/287.jhtml) is responsible for quality control and training for investigators.

Epidata (version 3.0) procedure will be used to restrict data values. Two trained investigators will enter and compare the data independently to rule out the difference.

### Statistical analysis

4.6

Trained statisticians will adopt intention-to-treat approach for effectiveness and safety analysis. In addition, the last-observation-carried-forward method will be applied in handling missing values. All statistical analysis will be conducted by Statistical Packages of Social Sciences (SPSS) software (version 22.0). Statistical test is two-sided and *P* < .05 is statistically significant. The mean ± standard deviation will be used for the description of continuous variables. The percentage is used to categorize the variable's description. Continuous variables following the normal distribution will be analyzed by Student *t* test; otherwise, non-parametric tests will be used to compare group differences.

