### Sample size calculation

2.5

We calculated the sample size according to our primary study which conducted from January 2018 to October 2018 into the efficacy of the HGWG versus HGWG placebo, and we found that patients taking HGWG achieved 83.5% ACR50, whereas patients in the placebo group achieved 54.7% ACR50 response. Formula of sample size calculation is . In this formula, N1 and N2 are the number of HGWG and placebo group, *u*_α/2_ = 1.96 when type 1 error is 0.05; *u*_β_ = 1.282 when type II error is 0.1 in two-sided tests. is the mean of *p*_1_ and *p*_2_.^[8]^ It was estimated that approximately 50 participants per group were needed to achieve 90% power and a (2-sided) 5% significance level in detecting treatment differences. We estimate that 120 patients (60 in each group) will be enrolled to ensure that the results are statistically significant, considering a reduction rate of 20%.

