### Primary outcome measure

4.1

ACR50 from baseline to 12 weeks after treatment will be compared. ACR50 is a standard to describe RA symptoms.^[9]^ ACR 50 is met when the number of tender joints reduces by ≥50%, the number of swollen joints by ≥50%, and at least 3 of the following 5 indexes improves by ≥50%:

Patient's assessment on arthritis pain using a Visual Analogue Scale (VAS) of 0 to 100 mmPatient's global assessment of disease activity using VAS scale (0–10)Patient's assessment of physical function and disability HAQ-DIErythrocyte sedimentation rate (ESR)C-reactive Protein (CRP) level

Similarly, ACR20 is met when ≥20% is achieved in the reduction of tender joint number, swollen joint number, and indexes of 3 of the 5 other measurements.^[10]^

ACR scale has been accepted as the efficacy benchmark in RA clinical trials and has greater discriminant capacity to distinguish patients on active treatment from placebo control.^[9,11,12]^ Here we choose ACR50 as the primary index for that ACR50 can provide more useful information than ACR 20/70.^[13,14]^

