### Secondary measurements

4.2

The secondary outcomes will be to compare the rates of change in the ACR20/70, DAS28, HAQ-DI, Patient Assessment of Arthritis Pain, Patient Global Assessment of Arthritis, and AIS score from baseline to 2 weeks, 4 weeks, 8 weeks, 12 weeks, 24 weeks’ and 48 weeks’ follow-up. The rate of change in the ACR50 from the baseline to 2 weeks, 2 weeks, 4 weeks, 8 weeks, 12 weeks, 24 weeks’ and 48 weeks’ follow-up are also secondary outcome measures. Additionally, the change in score on the 36-item Short-Form Health Survey Questionnaire (SF-36) from baseline to 4 weeks, 8 weeks, 24 weeks, and 48 weeks is also calculated.

The DAS28 is an index calculating the number of painful and swollen joints (28 joints, i.e. shoulders, elbows, wrists, metacarpophalangeal and proximal interphalangeal joints, and knees), ESR and the score of global assessment.^[15]^ The formula of DAS 28 is 0.56 × √(28 painful joint count) + 0.28 × √(28 swollen joint count) + 0.70 × (ln ESR) + 0.014 × GH. ESR refers to ESR. GH is the patient's general health visual analog scale (0–10 mm).^[16–18]^

HAQ-DI is a subscale of ACR 20/50/70 that reports biochemical and physical conditions. It has been widely used in RA clinical trials to assess disease activity and patient disability.^[19]^ The HAQ-DI measure shave eight dimensions of functional activity: pruning, dressing, rising, eating, walking, personal hygiene, reach, grip, and other routine activities. Each item has 4 degrees ranging from 0 to 3. “0” refers to “no functional difficulty”, “1” to a bit of functional difficulty, “2” to very much functional difficulty, and “3” to no ability to work. HAQ-DI score 0 to 1 means mild to moderate functional difficulty; 1 to 2 means moderate to severe disability; and 2 to 3 means generally severe disability.^[20]^

People with RA often have sleep disorders that worsen as RA deteriorates.^[10,21]^ The Athens Insomnia Scale (AIS) can help patients quantitatively self-evaluate sleep disorders with a psychometric instrument that includes eight indicators for sleep induction, awakenings during the night, final awakening, total sleep duration, sleep quality during the night, wellbeing during the night, functioning capacity during the day time, and sleepiness during the day time. The score for each indicator ranges from 0 to 3, and the total score is 24 points. The higher the score, the worse the sleep quality, and vice versa.^[22]^

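### LOCF as the only stated missing-data rule lets earlier visits decide week-12 ACR50 and puts on-treatment values into the off-treatment week-24 and week-48 comparisons

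*Protocol article*

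**What the plan says.** Section 4.6 of the protocol article (Statistical analysis) gives one rule for incomplete data: "the last-observation-carried-forward method will be applied in handling missing values". It stands beside the choice of population: "Trained statisticians will adopt intention-to-treat approach for effectiveness and safety analysis". The rule is not limited to any endpoint, visit or reason for missingness.

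The rule applies to the following design:

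- **Primary outcome (section 4.1):** "ACR50 from baseline to 12 weeks after treatment will be compared". Read with the Abstract, this is a yes/no response at week 12.
- **Visits (section 4.5):** weeks 2, 4 and 8 precede the primary assessment, and weeks 24 and 48 follow it.
- **Treatment period (section 4.5):** "participants will receive 12 weeks of medication and 36 weeks of follow-up".
- **Later comparisons (section 4.2):** ACR20/70, DAS28, HAQ-DI, pain, patient global assessment and AIS are compared out to week 48. For ACR50, "24 weeks’ and 48 weeks’ follow-up are also secondary outcome measures".
- **Expected loss (section 2.5):** the total of 120 was set "considering a reduction rate of 20" per cent.

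**The concern.** LOCF acts differently on the two kinds of comparison here.

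At week 12 it replaces a missing primary result with the status at the last visit attended. A patient who met ACR50 at week 4 and then left is scored as a week-12 success, whether the reason was a move, an adverse event or loss of effect. Success at week 12 then partly means success at some earlier visit, and how far it does so depends on who leaves each arm and when.

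At weeks 24 and 48 the patients are off study drug, and the purpose of those visits is to see whether any benefit lasts. For a patient last seen at week 12 or before, LOCF enters a value obtained on study drug. That presupposes the answer to the question.

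The primary test rests on 60 patients per arm, so a rule that fixes the result for a sizeable share of them can change the estimate and possibly the conclusion.

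**Working it through.** **Inputs from the document.** Section 2.5: "patients taking HGWG achieved 83.5% ACR50, whereas patients in the placebo group achieved 54.7% ACR50 response"; two-sided 5% level, 90% power, about 50 per group, 60 per group enrolled, 20% loss.

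**Inputs not in the document (assumptions).** Dropout by arm, and the share of dropouts who met ACR50 at their last visit. I take 50% on HGWG and 30% on placebo, then show a range.

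**1. The plan's own figure.** The usual two-proportion formula (pooled variance under the null, 1.96 and 1.282) with 0.835 and 0.547 gives 52.0 per group, which agrees with about 50. Power without loss is 88.8% at 50 per group and 93.7% at 60.

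**2. Patients affected at week 12.** 0.20 × 60 = 12 per arm. The document does not say by which visit the 20% is lost, so 12 applies if the loss has occurred by week 12.

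**3. Effect on the primary difference.** Let d be the loss in an arm, p the completers' response rate and q the share of dropouts responding at their last visit.

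- LOCF rate = (1 − d) × p + d × q
- Non-response rate = (1 − d) × p
- LOCF difference minus non-response difference = d₁q₁ − d₂q₂

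Equal loss, 20% in each arm:

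- LOCF: 0.8 × 0.835 + 0.2 × 0.5 = 0.768; 0.8 × 0.547 + 0.2 × 0.3 = 0.498; difference 27.0 points
- Non-response: 0.668 and 0.438; difference 23.0 points

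Loss of 30% on HGWG and 10% on placebo:

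- LOCF: 0.7 × 0.835 + 0.3 × 0.5 = 0.7345; 0.9 × 0.547 + 0.1 × 0.3 = 0.5223; difference 21.2 points
- Non-response: 0.5845 and 0.4923; difference 9.2 points

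Loss of 10% on HGWG and 30% on placebo:

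- LOCF: 0.9 × 0.835 + 0.1 × 0.5 = 0.8015; 0.7 × 0.547 + 0.3 × 0.3 = 0.4729; difference 32.9 points
- Non-response: 0.7515 and 0.3829; difference 36.9 points

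| Loss, HGWG / placebo | LOCF | Non-response | d₁q₁ − d₂q₂ |
|---|---|---|---|
| 20% / 20% | 27.0 | 23.0 | 0.10 − 0.06 = +4 points |
| 30% / 10% | 21.2 | 9.2 | 0.15 − 0.03 = +12 points |
| 10% / 30% | 32.9 | 36.9 | 0.05 − 0.09 = −4 points |

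**4. Range over the unknown q.** Set q = r × p in each arm, with r from 0 (no dropout responding when last seen) to 1 (dropouts responding as completers do). At r = 0 LOCF equals non-response. At r = 1 it returns the planning difference of 28.8 points.

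| Loss, HGWG / placebo | r = 0 | r = 0.5 | r = 1 |
|---|---|---|---|
| 20% / 20% | 23.0 | 25.9 | 28.8 |
| 30% / 10% | 9.2 | 19.0 | 28.8 |
| 10% / 30% | 36.9 | 32.8 | 28.8 |

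**5. Power at 60 per group.** With 20% loss in each arm, power rises from 72% at r = 0 to 94% at r = 1. With 30%/10% loss it runs from 17% to 94%.

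**6. Weeks 24 and 48.** No arithmetic is needed. Study medication ends at week 12, and the next visits are weeks 24 and 48. Under the stated rule, a patient last seen at or before week 12 has an on-treatment value at both later visits. A patient last seen at week 24 carries an off-treatment value to week 48, so this problem does not arise for that patient.

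**The case against.** The strongest reply is that the illustration sets LOCF against another convention, not against the truth. Counting missing as non-response answers a composite question in which being unobserved is itself a failure, and it too moves with unequal dropout: at 10%/30% loss it gives the larger difference. With equal loss, LOCF's 27.0 points lies below the 28.8 assumed in planning, so LOCF need not flatter the drug. All of this stands, and it is why the figures are illustrations and not estimates of bias.

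It is also fair that visit-specific rules and sensitivity analyses are often left to a full analysis plan. Their absence from a condensed article is not the complaint. The article states a rule without exceptions, and the complaint is about that rule.

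A reader might infer more than the document supports:

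- **That every dropout becomes a responder.** Only those who met ACR50 at their last visit do. The others are carried as non-responders, and those with baseline data only are carried as unchanged.
- **That LOCF must overstate durability.** Values are carried in both arms, early non-responders are carried as failures, and background DMARDs and NSAIDs are allowed. No direction is shown for the difference between arms.
- **That stopping study drug means missing data.** The document does not say so. Under intention-to-treat, such a patient may still attend visits.
- **That understated standard errors favour non-response.** Any single imputation, including non-response, treats filled-in values as observed.
- **That the trial dates make much of week 48 imputed.** Recruitment to 1 April 2021 (section 5.1) does conflict with final visits by 31 July 2021 (section 4.4). That is a separate matter. The number affected depends on an accrual pattern that is not given, and anyone enrolled by 13 February 2021 could still have an off-treatment week-24 value.

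**Conclusion.** The point holds and should be fixed. The stated rule lets an ACR50 response at week 2, 4 or 8 stand in for the week-12 primary result, for about 12 of 60 patients per arm if the planned 20% is lost by then. It also fills off-treatment comparisons with on-treatment values for anyone last seen by week 12.

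The size for the primary outcome depends on dropout by arm and on response at the last visit, neither of which the document gives. With the 50%/30% assumption, the choice of rule moves the difference by 4 points under equal 20% loss, and by 12 points upward or 4 downward in the two unequal patterns. The direction is therefore not established. The week-24 and week-48 part concerns secondary outcomes only, but it needs no dropout assumption beyond some patients being lost by week 12.

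**What to change.** Replace the LOCF sentence in section 4.6 with rules by type of outcome:

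- **Primary:** all randomised patients are analysed, and a missing week-12 ACR50 counts as non-response. Multiple imputation of the ACR components is the sensitivity analysis, because the non-response rule is itself sensitive to unequal dropout.
- **ACR20/50/70 at other visits:** the same non-response rule, for visits that were due.
- **Continuous outcomes:** a mixed model for repeated measures on observed data.
- **Weeks 24 and 48:** no value from week 12 or earlier is carried forward.

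The change is to analysis wording and needs no new patients or visits. It should be made before unblinding, so that the rule is not chosen with dropout by arm in view.

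The cost is lower reported response rates and lower power. With 20% loss in each arm and 60 per group, the expected rates are 66.8% and 43.8% and power is about 72%. Section 2.5 should therefore restate its 90% for this analysis.

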### Randomization and allocation

3.4

Shanghai Medical Clinical Research Center (CRC) will control the randomization develop a random number table by SAS9.1 PROC PLAN. The random number table will be generated in a ratio of 1: 1 using 3 test centers as a stratification factor. This table contains 2 corresponding groups, one is sequence number of inclusion, the other one is the treatment or placebo group.

Pharmaceutical factory will contact the CRC to obtain the random number table, then post the sequence number to boxed of medicine (HGWG or placebo) according to the table.

When a participant is recruited in, the investigator will make a central telephone call and give him/her the medicine (HGWG or the placebo) from the administrator according to the central call.

All the investigators except for the CRC and pharmaceutical factory will not know the corresponding relations between sequence numbers and different groups until the trials completed.

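### Randomisation is stratified by centre and baselines are collected, but the tests named for continuous outcomes use neither; this loses precision without making the analysis invalid

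*Protocol article*

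**What the plan says.** All references are to the Protocol article.

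- **Section 3.4, Randomization and allocation:** "The random number table will be generated in a ratio of 1: 1 using 3 test centers as a stratification factor".
- **Section 4.1, Primary outcome measure:** "ACR50 from baseline to 12 weeks after treatment will be compared". ACR50 is a yes/no response.
- **Section 4.2, Secondary measurements:** "The secondary outcomes will be to compare the rates of change in the ACR20/70, DAS28, HAQ-DI", followed by pain, patient global assessment and AIS, at each visit from week 2 to week 48. Change in SF-36 is added at weeks 4, 8, 24 and 48.
- **Section 4.5, Data collection and monitoring:** baseline plus six later assessments.
- **Section 4.6, Statistical analysis:** "Continuous variables following the normal distribution will be analyzed by Student *t* test"; "otherwise, non-parametric tests will be used to compare group differences". For categorical variables it gives only a description: "The percentage is used to categorize the variable's description". On significance: "Statistical test is two-sided and *P* < .05 is statistically significant".

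Section 4.6 mentions no centre term, baseline covariate or model.

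**The concern.** The design pays for two sources of precision. Allocation is balanced within centre, and each continuous outcome has a baseline measurement. A two-sample t test or a rank test uses neither as a covariate.

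Three consequences follow for the continuous secondary outcomes (DAS28, HAQ-DI, pain, patient global, AIS, SF-36).

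1. The treatment difference is estimated with more variance than necessary.
2. A chance difference between the arms at baseline leaves a residual effect on the comparison.
3. Which test is used, and so whether the result concerns a mean difference or ranks, depends on a check of the observed distribution.

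For the ACR responses, an analysis that leaves out the stratification factor overstates the standard error when response rates differ between centres. The test then becomes conservative. At stake is efficiency, not a raised false-positive rate.

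**Working it through.** **The plan's own figure.** Section 2.5 gives ACR50 rates of 83.5% and 54.7%, normal quantiles 1.96 and 1.282, and the mean of the two rates (0.691). The pooled two-proportion formula gives

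n = [1.96 × √(2 × 0.691 × 0.309) + 1.282 × √(0.835 × 0.165 + 0.547 × 0.453)]² / 0.288² = (1.281 + 0.796)² / 0.0829 ≈ 52 per group,

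close to the stated figure of about 50. The planned 60 per group is 50 × 1.2. The sizing is therefore an unadjusted comparison of two proportions.

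**Continuous outcomes: variance.** Assume equal variance σ² at baseline and follow-up, with correlation r. The documents give no r, so 0.3 to 0.7 is an assumed range. Per-patient variances are:

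- change score: 2σ²(1 − r)
- follow-up value alone: σ²
- ANCOVA: σ²(1 − r²)

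Hence ANCOVA / change score = (1 − r²) / [2(1 − r)] = (1 + r)/2, and ANCOVA / follow-up alone = 1 − r².

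| r | vs change-score t test | vs follow-up-only t test |
|---|---|---|
| 0.3 | 0.65 | 0.91 |
| 0.5 | 0.75 | 0.75 |
| 0.7 | 0.85 | 0.51 |

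**Continuous outcomes: baseline imbalance.** Under the same assumptions, a chance baseline difference d between arms shifts the expected change-score difference by (r − 1)d. That is −0.7d, −0.5d and −0.3d for r = 0.3, 0.5 and 0.7: partial, and opposite in sign to d. Adjusting for baseline removes it.

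**ACR50: variance.** The documents give no centre-specific rates, so these are assumed, with 20 patients per arm in each of three centres. The unstratified variance term is 0.835 × 0.165 + 0.547 × 0.453 = 0.3856. Stratifying removes the between-centre variance of the rates.

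- Placebo ±10 points, HGWG ±5: (0.3856 − 0.0083) / 0.3856 = 0.978
- Placebo ±15, HGWG ±10: (0.3856 − 0.0217) / 0.3856 = 0.944
- Placebo ±20, HGWG ±14.5: (0.3856 − 0.0407) / 0.3856 = 0.894

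**ACR50: simulation.** Each scenario used 100,000 runs with three equal centres. Centre effects were set on the log-odds scale, with the average rates held at 54.7% and 83.5%. Each cell gives the unadjusted chi-square test, then the centre-stratified Mantel-Haenszel test.

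| Placebo rates by centre (%) | Power, 60 per arm (%) | Power, 48 per arm (%) | Type I error, 60 per arm (%) |
|---|---|---|---|
| 54.7 / 54.7 / 54.7 | 94.1, 93.8 | 88.4, 88.0 | 5.3, 5.3 |
| 42.5 / 54.9 / 66.7 | 94.5, 94.6 | 88.7, 88.9 | 4.8, 4.9 |
| 31.4 / 55.5 / 77.2 | 95.2, 96.2 | 89.7, 91.3 | 3.7, 4.9 |
| 22.4 / 56.4 / 85.3 | 96.1, 97.7 | 91.1, 94.2 | 2.4, 4.9 |

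The 48 per arm column is 60 less the 20% loss (60 × 0.8). The gain at 60 per arm runs from −0.3 to +1.6 power points. It reaches about 3 points at 48 per arm under the widest spread.

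**The case against.** The strongest defence is that section 4.6 is one paragraph of a condensed article, and that strata terms, covariates and model form are commonly left to an analysis plan, which is not shown here. This holds for the ACR50 test: its absence from the article is not an error in itself. It holds less well for the continuous outcomes, where the article does commit to a method, and an analysis plan that followed it would inherit unadjusted tests. That each visit is tested separately is likewise an inference from section 4.2; section 4.6 does not say so.

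Several stronger readings are tempting but unsupported.

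- **A reader might infer that a t test or rank test is assigned to ACR50.** The sentence is about continuous variables, and section 2.5 sizes the trial on two proportions. The document names no test for ACR50; it does not name a wrong one.
- **A reader might infer that baseline imbalance carries over in full.** A change score already subtracts baseline, so only (r − 1)d remains.
- **A reader might infer that the choice between two tests leaves the result open to selection.** The rule is stated in advance. The normality criterion and the rank test are unnamed, which is a detail an analysis plan can settle.
- **A reader might infer that the primary analysis is seriously weakened, or that fewer patients would do.** The ACR50 loss is nil to small. The larger precision figures concern secondary outcomes, and the sample size was set on ACR50.

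It is also fair to say that strong centre differences are not evident from the documents: all three hospitals are in one city.

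**Conclusion.** The point holds as one of efficiency. As written, the named tests for continuous outcomes leave out both the stratification factor and the baseline covariate. Against a change-score t test, baseline adjustment saves 15 to 35% of the variance over the assumed range of r; against a follow-up-only t test it saves 9 to 49%. These figures assume equal variances at baseline and follow-up. The further gain from a centre term in the continuous models was not quantified, since no centre data are given.

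For ACR50 the case for stratifying rests mainly on matching analysis to design. The gain in power is absent when centres are alike and about 1 to 2 points at 60 per arm when they differ strongly. Under the two widest assumed spreads, the unadjusted test's type I error falls to 3.7% and 2.4%, while the stratified test stays at 4.9%. The unadjusted analysis would be conservative, not invalid.

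**What to change.** **Continuous outcomes** (DAS28, HAQ-DI, pain, patient global, AIS, SF-36): replace the t test and rank test rule with ANCOVA at the visit of interest, adjusted for baseline value and centre. Alternatively, use one repeated-measures mixed model with treatment, visit, treatment-by-visit, baseline value and centre, over the visits at which each outcome is collected. Keep rank tests as a sensitivity analysis, named in advance and not triggered by a normality check. If the mixed model is chosen, the last-observation-carried-forward statement in section 4.6 needs to be reconciled with it, because such a model is fitted to the observed visits.

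**ACR20/50/70:** state a Cochran-Mantel-Haenszel test stratified by centre, with the stratified risk difference and its 95% confidence interval.

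**Cost:** analysis wording only, to be settled before unblinding. Centre and baseline values are already collected, so no visit, procedure or patient is added and the planned 120 stands. The statistician should confirm that the named SPSS version produces the stratified risk difference with its interval, or name other software for that step.
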